## Abstract

**Background:**

Hearing impairment (HI) is a common sensory deficit with considerable impacts on social well-being (SWB) in adults. Evidence on the effectiveness of auditory rehabilitation and hearing health education in the social domain of health for individuals with HI is scarce.

**Objective:**

This study aims to test the feasibility and efficacy of providing free hearing aids or a combined offline and online hearing health education intervention on social isolation and functioning among Chinese adults with HI.

**Methods:**

This study is a 3-arm, single-blinded, randomized controlled trial (RCT) with a follow-up at 24 months after the baseline study. A total of 435 participants aged 18 years and older with some degree of HI will be recruited and randomly assigned to 2 intervention groups and 1 control group. Free hearing-aid provision, as well as a hearing health education program that is combined with online and offline lessons, will be implemented in 2 intervention groups, respectively. The control group will not receive any intervention. The primary outcomes include social isolation and functioning in society. The secondary outcomes include social engagement, a sense of mastery, self-efficacy, psychological resilience, chronic diseases, life satisfaction, hearing health literacy, and hearing care usage.

**Results:**

Participants were recruited for hearing tests in September 2022, during which baseline results were collected through in-person interviews. Follow-up interviews were conducted in September 2024. The primary analysis will use ANOVA, linear mixed-effects modeling, structural equation modeling, and cost-effectiveness analysis.

**Conclusions:**

The findings of this study will provide evidence for the impact and cost-effectiveness of a community-based auditory or hearing health education intervention on SWB among Chinese adults with HI, which may contribute to promoting hearing health and reducing adverse health consequences in an aging society.

**Trial Registration:**

Chinese Clinical Trial Registry ChiCTR2200062148; https://www.chictr.org.cn/showproj.html?proj=174741

**International Registered Report Identifier (IRRID):**

DERR1-10.2196/64115

## Introduction

### Background

Hearing impairment (HI) significantly impacts the health and well-being of adults, especially middle-aged and older individuals. Globally, approximately 1.57 billion people had some degree of HI in 2019, with nearly 30% suffering from disabling HI and the majority of whom were aged ≥45 years [1]. HI is associated with various negative consequences, including declines in physical and cognitive functions, increased depression and anxiety, and heightened risks of frailty, hospitalization, and mortality [2-7]. Unaddressed HI often leads to significant withdrawal from the social domain of life and poor performance of functioning in society.

Social well-being (SWB) not only encompasses one’s ability to establish healthy relationships and engage meaningfully with social networks but also represents a subjective evaluation of personal life circumstances and functioning in society [8]. The World Health Organization (WHO) identifies SWB as a crucial element for overall health and has prioritized it worldwide to enhance social connections to fight against social isolation, which is often regarded as a common reflection of poor SWB [9]. Social isolation, defined as an objective absence or paucity of contacts and interactions between a person or within a social network [10,11], is associated with HI and is often considered a potential pathway to adverse health outcomes related to HI [12]. Communication difficulties or mental fatigue attributed to HI, as well as the increased cognitive load required to compensate for auditory deficits often discourage social interactions among those with HI [13-15].

Compared to social isolation, functioning in society is a broader and more comprehensive measure for assessing one’s capacity to interact with others, contribute to various societal roles, and actively engage in meaningful activities, including but not limited to work, education, family life, and community involvement. The International Classification of Functioning, Disability and Health (ICF), provides a framework for assessing functioning in society across three levels: the body or body part, the whole person, and the whole person in a social context, corresponding to its definition of functioning encompassing all body functions, activities, and participation [16]. Activity limitations and participation restrictions, which measure functions from both individual and societal perspectives, refer to a person’s capacity in a standard environment and performance in a normal environment under healthy conditions. The validation of the ICF application for adults with HI and in audiological or rehabilitation research has been examined internationally [17,18], demonstrating a positive association between hearing loss and decline in mobility, self-care, or the ability to get along with others [2,19,20]. Despite evidence supporting HI as a modifiable risk factor for social health, the efficacy of HI interventions in enhancing SWB requires further research [21,22]. Previous studies either have shown mixed results with little consistency in the significance and magnitude of the effectiveness of hearing intervention on social isolation or functioning [13,23-25], or used small sample sizes, and nonrandomized controlled trials to identify the causal relationships between hearing intervention and improvements in SWB [13,26,27]. Furthermore, few interventional studies have further discussed and tested the possible mechanistic pathway through psychosocial or supportive factors, and evidence regarding middle-income countries is scarce.

### Conceptual Framework and Interventions

Both the ICF and stress-buffering models provide insights into how adult-onset HI affects SWB and the effectiveness of auditory interventions. The ICF describes the bidirectional association among impairments, activity limitations, and participation restrictions. Besides, functioning can be viewed as the outcome of interactions between health conditions and contextual factors, which include external environmental factors (eg, supportive environment or social attitudes) and internal personal factors (eg, coping style and psychological resources) [16]. The ICF reveals that the ideal interventions should consider a holistic approach combining physical, personal, and environmental factors. The stress-buffering model, derived from the stress process paradigm, posits that social and coping resources can buffer (mediate or moderate) the impacts of stressors such as HI on health and well-being by altering one’s appraisal and coping behaviors toward a stressor or threat [28,29]. Empirical studies support the potential psychological resilience to mediate the relationship between functional HI and SWB [14].

Intervention strategies typically focus on individual or environmental approaches. Individual strategies such as audiological training, skill development, and health education aim to use residual hearing through individually tailored intervention and improve communication and coping skills for persons with HI or their communication partners (CPs). Skill development and health education are person-centered approaches that can be widely promoted and implemented at the community level. Either an appropriate use of hearing aids or assistive devices to compensate for auditory loss, the development of self-management skills for HI, or the application of positive communications, are often considered potential effective skill-developing interventions. Educative interventions in the hearing rehabilitation context empower adults with HI and their CPs to adapt to hearing deficits and improve help-seeking behaviors. Hearing health education (HHE) involves the dissemination of knowledge about the nature of hearing and hearing loss, communication strategies, the promotion of hearing devices or assistive technologies use, and the enhancement of psychosocial resources. Environmental strategies center on enhancing support systems within micro and meso environments, such as family and community, by providing information and guidance to the significant others and helping them better understand the challenges faced by adults with HI, as well as fostering active communication skills, awareness, and access for hearing health care.

In response to the WHO’s guidelines on integrated person-centered ear and hearing care (IPC-EHC), we initiated the HISEA (Hearing Impairment and Social Outcomes Evaluation in Adults) project to conduct hearing interventions that targeted the social isolation and functioning of HI persons in Guangdong Province, China. This community-delivered intervention aligns with the China Disability Action Plan (2021-2025), which emphasizes the importance of raising public awareness of hearing prevention and care through health education as well as treating HI through rehabilitative services. Figure 1 presents a diagram illustrating how the interventions developed in HISEA align with the ICF and stress-buffering framework.

**Figure 1 figure1:**
[figure not shown]
The theoretical framework of Hearing Impairment and Social Outcomes Evaluation in Adults developed based on the International Classification of Functioning, Disability and Health and stress-buffering model. HI: hearing impairment; ICF: International Classification of Functioning, Disability and Health; KAP: Knowledge, Attitude, and Practice Theory.

### Study Aims and Hypotheses

This full-scale randomized controlled trial (RCT) aims to evaluate the feasibility and efficacy of a community-delivered hearing aid provision and HHE program in improving social health among hearing-impaired adults in China. The key outcomes are social isolation and societal functioning. In addition, it seeks to determine if psychosocial factors and social support buffer the HI-SWB linkage as well as the effects of hearing interventions on social health.

We hypothesize there will be positive effects after the long-term interventions of HAU and HHE on hearing-impaired older adults’ social health, and strengthened psychological well-being could be potential pathways.

## Methods

### Overview

This protocol was developed on the basis of the theoretical framework in Figure 1 and is reported according to the Standard Protocol Items for Interventional Trials (SPIRIT) [30,31]. A peer review report can be found in Multimedia Appendix 1, and a SPIRIT checklist can be found in Multimedia Appendix 1.

### Feasibility Study

Before the initiation of the full-scale RCT, a feasibility study was undertaken. This study involved a comprehensive review and evaluation of the overall implementation plan by community social workers and audiologists to ascertain its feasibility from a health care professional perspective. In addition, a cohort of 28 adults with HI was recruited from Zhaoqing City, Guangdong Province, to conduct hearing checks and baseline interviews. During this process, we evaluated the participants’ willingness to engage in the study, confirmed their comprehension of the survey questionnaires, and assessed their readiness to participate in health education initiatives or to wear hearing aids over a long period, should they be assigned to the treatment groups. We made some adjustments to the questionnaire based on the feedback from the respondents. The preliminary results validated the feasibility of our intervention study.

### Study Design and Setting

A three-arm, single-blinded RCT with a 24-month follow-up period will be conducted. A total of 435 eligible participants were randomly assigned in a 1:1:1 ratio to a control group, a hearing aid use (HAU) group, or an HHE group. The HAU group will receive hearing aids and follow-up instructions. Due to budget constraints, the audiological rehabilitation intervention predominantly used hearing aids provided by the Audiology Department of the Guangdong Provincial Cultural Sports and Rehabilitation Assistive Devices Center for People with Disabilities (GPSRC), which is affiliated with the China Disabled Persons’ Federation (CDPF). Individuals diagnosed with disabling HI and classified as persons with hearing disability are eligible to apply for complimentary hearing aids and fitting services from the local CDPF departments. Since the number of adults with HI who were eligible for hearing-aid fitting was limited to one site at the time of the baseline survey and intervention, a total of 139 persons with disabled HI were randomly selected from 4 sites with similar socioeconomic and cultural conditions. The selection was based on the list provided by GPSRC, which maintains records of hearing-disabled persons in Guangdong Province. The HHE group will undergo both offline and online educational interventions, while no interventions are planned for the control group that is similar to a natural setting. A sample of 278 adults diagnosed with some degree of HI was randomly selected and assigned to the HHE group and control group from Hualong County in Guangzhou, Guangdong, based on its roster. For the HAU group, participants were prescribed hearing aids at baseline (T0) and received reinstruction on the use of hearing aids 12 months after T0. For the HHE group, participants were required to participate in an offline hearing education at T0, followed by an online educational intervention at 6 months after T0, and an offline information intervention at 12 months after T0. The primary outcomes are social isolation and functioning, assessed at baseline and 24 months.

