### Randomization, Allocation, and Masking

After confirming eligibility and informed consent, participants are randomly stratified by HI severity and the field site to ensure a balanced distribution of participants. Randomization is performed by an independent statistician who is not involved in data collection, management, or analysis using a computer-generated random number sequence to assign participants to either the treatment or control group [35]. Allocated interventions will not be modified unless participants voluntarily withdraw for personal reasons. Due to the nature of the interventions, complete blinding of participants and facilitators is not feasible. However, we minimize the potential biases by blinding participants to the study hypothesis, using standardized protocols for training and tools for measurement, and masking field staff to allocation details.

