Third, the provision of free hearing aids may raise concerns regarding the social approval effect. Previous research on hearing aid interventions has typically involved the distribution of free devices [51,58,59]. In instances where there is a financial burden associated with acquiring commercial hearing aids, selection bias may arise, as economically disadvantaged older individuals may find it more challenging to participate in such interventions. The Chinese government has established a range of welfare policies aimed at supporting individuals with disabilities and the elderly, which include not only rehabilitation services, but also living subsidies for disabled individuals, long-term care insurance, and older adult care subsidies. Within this welfare framework, hearing aids do not represent a unique benefit. Therefore, we contend that the social approval effect remains within a manageable scope and is unlikely to compromise the reliability and validity of the RCT. Future research could also compare the intervention effects of paid hearing aids with those of free hearing aids.

Fourth, the interventions are conducted at different sites, which may result in geographical and selection biases. Nevertheless, the comparable socioeconomic and cultural contexts of these sites are expected to alleviate such biases. There was no pilot study due to time and budget constraints; however, given that the social and demographic characteristics of the feasibility study site closely resemble those of the formal trial sites, we believe this limitation does not pose a significant threat to the research design.

Fifth, our reliance on self-reported measures of social isolation and functioning may introduce measurement bias, which we will address through the use of validated tools, cross-validation, and multisource evaluations.

Lastly, although the sample size was determined using standard calculation methods, it remains relatively small, which affects its representativeness and external validity. Randomization in a small sample may not completely eliminate the preexisting differences either. Therefore, we will further use matching techniques or other econometric methods during the statistical analyses.

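### As the protocol describes recruitment, the hearing-aid arm came from a different source population from the controls, so the only powered contrast is not a randomised comparison although it is planned as one

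*Protocol article*

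**What the plan says.** Study Design and Setting opens with full randomisation: "A total of 435 eligible participants were randomly assigned in a 1:1:1 ratio to a control group, a hearing aid use (HAU) group, or an" (the sentence closes by naming the education arm). Randomization, Allocation, and Masking adds that "participants are randomly stratified by HI severity and the field site to ensure a balanced distribution of participants".

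Study Design and Setting then describes two recruitment streams.

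- **HAU.** "a total of 139 persons with disabled HI were randomly selected from 4 sites with similar socioeconomic and cultural conditions". The sampling frame is a disability register: "The selection was based on the list provided by GPSRC, which maintains records of hearing-disabled persons in Guangdong Province". The reason given begins "Since the number of adults with HI who were eligible for hearing-aid fitting was limited to one site at the time of the baseline survey".
- **HHE and control.** "A sample of 278 adults diagnosed with some degree of HI was randomly selected and assigned to the HHE group and control group", the source being the Hualong County roster.

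The Sample Size section powers the trial on HAU versus control only (WHODAS 2.0 change from baseline at 24 months, standardised effect 0.404). Statistical Analysis plans intention-to-treat comparisons by ANOVA and linear mixed models and names no adjustment covariates. The weighting and matching mentioned there are for missing data and attrition.

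Limitations concedes possible geographical and selection bias because the interventions run at different sites, but holds that "the comparable socioeconomic and cultural contexts of these sites are expected to alleviate such biases". It attributes remaining differences to randomisation in a small sample and mentions matching or other econometric methods in general terms.

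**The concern.** Random selection from a list is random sampling. It is not random allocation between treatments. If HAU participants were drawn from a register of people with disabling hearing loss, and controls from a county roster of people with any degree of loss, no chance mechanism decided who got hearing aids rather than nothing. Severity, disability registration and, at least in part, place then go with the arm.

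Stratified randomisation balances arms only within strata from which every arm can be drawn. It cannot balance arms that were filled from separate frames.

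At stake is what the trial may claim. An ANOVA or mixed model of HAU versus control would estimate the treatment effect plus whatever follows from registration, severity, poverty and place, under an RCT label. No other contrast has a sample-size basis.

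**Working it through.** **1. The plan's own sample size.** Inputs (Sample Size section): effect 0.404 SD, power 85%, 5% significance (two-sided reproduces the figure; one-sided would give 89).

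n per arm = 2(z₀.₉₇₅ + z₀.₈₅)² / d² = 2(1.960 + 1.036)² / 0.404² ≈ 110.02, rounded up to 111; the t-test solution is 110.99. This matches the stated 111 per group.

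With 20% inflation: 111 / (1 − 0.20) = 138.75, so 139. That is the number selected for HAU, and 2 × 139 = 278 is the number selected for HHE plus control. The counts fit quotas filled arm by arm. As a separate inconsistency, 139 + 278 = 417, not 435, and the enrolled arms are 121, 158 and 156.

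**2. The two streams side by side** (Study Design and Setting).

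| | HAU | HHE and control |
|---|---|---|
| Frame | provincial list of hearing-disabled persons | Hualong County roster |
| Hearing loss | disabling | any degree |
| Place | 4 sites | one county |
| Arms open to the person, as described | HAU | HHE or control |

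The Control Group section adds that a disability certificate must be actively sought and is a prerequisite for subsidised aids. Registration is therefore itself a selection process.

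**3. Baseline, HAU versus control** (Table 2). For proportions, SMD = (p₁ − p₂) / √{[p₁(1 − p₁) + p₂(1 − p₂)] / 2}. For age, the denominator is √{(SD₁² + SD₂²) / 2}. P-values are from Pearson chi-square and Welch t tests.

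| Variable | HAU | Control | SMD | p |
|---|---|---|---|---|
| Poor economic status | 96/120 = 80.0% | 39/154 = 25.3% | 1.31 | 3×10⁻¹⁹ |
| Chronic disease | 44/114 = 38.6% | 88/110 = 80.0% | −0.93 | 3×10⁻¹⁰ |
| Age, mean (SD) | 67.02 (11.75) | 74.82 (9.29) | −0.74 | 8×10⁻⁹ |
| Row labelled male | 75/121 = 62.0% | 56/156 = 35.9% | 0.54 | 2×10⁻⁵ |

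Worked example, economic status: (0.800 − 0.253) / √[(0.160 + 0.189) / 2] = 0.547 / 0.418 = 1.31.

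Two cautions. Chronic disease is missing for 156 − 110 = 46 controls. The sex totals (247 male, 187 female) are reversed against the arm counts, which sum to 56 + 56 + 75 = 187 and 100 + 101 + 46 = 247; the gap is the same size under either labelling.

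**4. HHE versus control.** These arms share a roster and are close on sex (SMD −0.005), economic status (0.10) and chronic disease (−0.17). They are not close on age (71.44 vs 74.82, SMD −0.42, p = 0.0002) or good self-rated health (149/157 = 94.9% vs 76/156 = 48.7%, SMD 1.20).

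**5. Illustration of the consequence.** The documents give no bias figure. Assume a residual HAU–control difference b in 24-month change and no treatment effect. With SE = √(1/121 + 1/156) = 0.121 SD, the rejection rate is 1 − Φ(1.96 − b/SE) + Φ(−1.96 − b/SE).

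| Assumed b (SD) | 111 vs 111 | 121 vs 156 |
|---|---|---|
| 0.1 | 11.6% | 13.1% |
| 0.2 | 31.9% | 37.9% |
| 0.3 | 60.8% | 69.7% |

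**The case against.** The article asserts randomisation several times: in the design sentence, the randomisation section, the eligibility criteria and the trial status. That no HAU participant was randomised against a control is therefore an inference from the recruitment account. This stands: the document contradicts itself, and only the investigators can say which account is right.

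The article also discloses site and selection bias, mentions matching, and collects relevant covariates; details may sit in an unseen analysis plan. This stands in part. Disclosure does not change the RCT label, and tracing the differences to small-sample randomisation names the wrong cause if the two streams are real.

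A reader might infer more than the text supports:

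- *That the four HAU sites exclude Hualong, so arm and site coincide fully.* The text says only that there were four sites. If Hualong is one of them, site overlap is partial; the difference in frame and severity definition remains.
- *That HAU has no one with mild loss.* Table 2 gives no audiometry by arm, and no threshold for disabling loss is stated.
- *That Table 2 disproves the claim of comparable sites.* It compares individuals by arm, and economic status is self-rated. It shows arm imbalance and cannot test site contexts.
- *That the bias can be computed from one covariate.* The powered endpoint is change from baseline, so stable level differences cancel. HAU participants are poorer but also younger and have less recorded chronic disease, so even the direction is open.

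Finally, the HHE–control gap in self-rated health shows that large imbalance is not confined to the HAU arm. Table 2 alone therefore does not isolate the cause; the recruitment account carries the argument.

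**Conclusion.** The point holds as a contradiction with consequences. Taken at its word, the recruitment description makes HAU versus control, and likewise HAU versus HHE, non-randomised, and it cannot be squared with 1:1:1 allocation stratified by severity and site. Baseline gaps of 0.54 to 1.31 SD on four variables are not plausible under random allocation and agree with that reading.

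The bias in 24-month change is unknown in size and sign. The rejection rates of about 13%, 38% and 70% rest wholly on the assumed 0.1, 0.2 and 0.3 SD and show sensitivity only. No increase in sample size would remove such a bias. Nor should HHE versus control be taken as the sound randomised contrast until its allocation is confirmed.

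**What to change.** 1. Reconcile Study Design and Setting, the randomisation section and Limitations, stating for each arm the sampling frame, the sites and how allocation was made.
2. Unless the two-stream account is wrong, describe HAU versus control and HAU versus HHE as non-randomised, withdraw the 1:1:1 and stratified-randomisation claims for HAU, and limit the causal claim.
3. For the HAU contrasts, replace the unadjusted ANOVA as primary with one pre-specified confounder-adjusted analysis. Propensity or overlap weighting plus regression is one reasonable choice among several. Use baseline outcome, better-ear pure-tone average, age, sex, economic status, self-rated health and chronic disease, and state how missing chronic-disease data are handled.
4. Report an overlap check on pure-tone average, balance after adjustment, effective sample size, and a sensitivity analysis for unmeasured site and registration effects.
5. Confirm how HHE and control were allocated before calling that contrast randomised, and explain the differences in self-rated health and age.

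This needs revised wording and a re-specified analysis but no new data, and the article says intervention effects are still unknown. The price is a weaker claim and a smaller effective sample for HAU.

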### Sample Size Calculation and Recruitment

Sample size calculations are based on the expected effects of the hearing aid intervention on the primary outcome: an individual’s functioning in society measured by the World Health Organization Disability Assessment Schedule 2.0 (WHODAS 2.0), which was developed within the ICF conceptual framework [34]. We estimate that a sample size of 222 (111 participants in each group) provides 85% statistical power with a 5% significance level to detect a standardized effect size of 0.404 for the difference between the HAU group and the control group in the mean change from baseline in the functioning score at the 24-month follow-up [23]. Since there is little evidence evaluating the effects of HAU on social isolation using the Lubben Social Network Scale (LSNS), or the effectiveness of HHE on functioning and social isolation, we will assign the HHE group the same sample size as the HAU group and the control group. To account for a 20% drop-in (uptake of hearing aids in the control group) and dropout (discontinuation of HAU in the hearing intervention group) rate, a total of 435 individuals are included. This comprises 121 individuals in the HAU group, 158 in the HHE group, and 156 in the control group, respectively. Recruitment activities are conducted in communities and villages (n=8) from Guangzhou, Shanwei, Chaozhou, and other areas in Guangdong Province, China. The recruitment of participants commenced on September 1, 2022, and was completed on September 31, 2022. Oral informed consent is obtained through prescreening, and written informed consent is presented by the investigator to the participant before the hearing screening. Hearing screening and assessment will be undertaken by an audiologist following a standardized procedure (Table 1).

**Table 1 table1:** Schedule of enrollment, interventions, and assessments.

Time point				Study period																												
				Enrollment T_1_						Allocation T_0_					Postallocation T_1_							Postallocation T_2_						Close-out T_4_				
				–30 to –1 Day						Day 0					6 months							12 months						24 months				
				T^a^		T^b^		C^c^		T	T		C		T		T		C		T			T		C	T			T		C
Enrollment																																
Eligibility screen				✓		✓		✓																								
Informed consent				✓		✓		✓																								
Demographics				✓		✓		✓																								
Health history				✓		✓		✓																								
Visual status				✓		✓		✓																								

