The HHE intervention consists of three parts. Part A is an interactive, face-to-face session consisting of a hearing health lesson and counseling for participants with HHE and community workers. Brochures for participants and their CPs or family members, and posters for community health education boards are provided. The hearing health lesson is taught by the program coordinators with a written lesson plan and prepared with easily accessible teaching materials, such as paper-based visual aids or slides. Part B is an internet-based educational section that aims to reinforce the content covered in Part A through the use of the WeChat public account. It was conducted 6 months after the baseline survey targeted adults with HI and their CPs. Part B consists of a 2-week online information support program delivering knowledge on hearing health and its consequences, positive skills and strategies for interacting with adults with HI, hearing prevention and rehabilitation guidance, and social support for adults with HI through textual, image, and video formats. All interventional-related information is disseminated through the WeChat public account registered by the research team. To ensure the accessibility and reach of online information support, the research team set up a check-in task and regularly reminded the procedure. Part C is an offline information provision that was conducted 12 months after the baseline survey with the purpose of reinforcing content in Part A and Part B. Hearing health educational pamphlets are designed for all the intervention objectives and are delivered to them accordingly. The content presented in the lessons, brochures, posters, a WeChat public account, and pamphlets is based on and adapted from the WHO Hearing Report (2021) and other relevant publications [37,38]. During the design phase of the intervention, the HHE intervention settings were discussed and deliberated with experienced audiologists, community workers, and community-dwelling adults with HI who would not participate in the study. It is deemed acceptable for adults with HHE and their CPs in the community.

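### HHE and control differ at baseline by more than the stated individual randomisation would plausibly produce; the cause is not established, so the actual allocation must be audited and stated

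*Protocol article*

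**What the plan says.** Study Design and Setting states that "A total of 435 eligible participants were randomly assigned in a 1:1:1 ratio to a control group" and two intervention arms. The HHE and control arms come from one roster: a sample of "adults diagnosed with some degree of HI was randomly selected and assigned to the HHE group and control group from Hualong County". The section on randomisation names the individual as the unit. It says that "participants are randomly stratified by HI severity and the field site to ensure a balanced distribution of participants", with an independent statistician "using a computer-generated random number sequence to assign participants to either the treatment or control group".

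The HHE section lists community residents and community workers among those the programme targets, beside participants and their families. On materials it says: "Brochures for participants and their CPs or family members, and posters for community health education boards are provided".

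Under Limitations, the protocol says that the interventions run at different sites. It adds that "Randomization in a small sample may not completely eliminate the preexisting differences either", and proposes matching or other econometric methods in response.

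**The concern.** HAU participants came from a separate disability register at four sites, so HHE against control is the contrast with the best claim to randomisation. If the groups were formed as described, baseline differences should be of chance size. Several are not.

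Self-rated health is close in concept to WHODAS functioning, a primary outcome. If the recorded difference is real and left unadjusted, part of it would be credited to HHE.

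The unit of allocation matters for a second reason, because part of HHE reaches beyond its participants. If both arms live in the same villages, controls may be exposed and the effect diluted. If whole villages were allocated, individual-level standard errors are too small. The protocol does not list communities by arm, so a reader cannot tell which risk applies.

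**Working it through.** **The plan's own figure.** The protocol states that "a sample size of 222 (111 participants in each group) provides 85% statistical power with a 5% significance level". The target behind it, set for HAU against control, is a standardised difference of 0.404. Two-sided, n per group = 2(1.960 + 1.036)²/0.404² = 110.02, rounded up to 111. Allowing 20% loss, 111/0.8 = 138.75, or 139 per arm, and 2 × 139 = 278 for HHE plus control. The figure reproduces for individually randomised participants and has no allowance for clustering. Actual enrolment was 158 HHE and 156 control.

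**Baseline, HHE against control (Table 2).**

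- *Self-rated health good:* 149 of 149 + 7 + 1 = 157, against 76 of 76 + 65 + 15 = 156. Chi-square = 313 × (76×8 − 80×149)² / (156×157×225×88) = 82.6 on 1 df, p about 1e-19. The difference is 94.9% − 48.7% = 46.2 points. The standardised difference is 0.462/√[(0.250 + 0.048)/2] = 1.20. For scale, the pooled proportion is 225/313 = 0.719 and the standard error of a chance difference is √[0.719 × 0.281 × (1/156 + 1/157)] = 0.051. Chance alone would keep the difference within about ±10 points in 95% of randomisations. The row adds to its printed totals (277, 118, 39), so no misprint is evident there.
- *Age, mean:* 74.82 − 71.44 = 3.38 years. The standard error is √(9.29²/156 + 6.51²/158) = 0.906, so Welch t = 3.73, p = 0.0002, standardised difference 0.42.
- *Age, spread:* variance ratio 9.29²/6.51² = 86.30/42.38 = 2.04, p about 1e-5.
- *Missing chronic-disease status:* arm size minus the row's count gives 156 − (22 + 88) = 46 in control (29.5%) and 158 − (39 + 105) = 14 in HHE (8.9%). Chi-square 21.6, p about 3e-6.
- *Compatible with chance:* sex p = 0.97, education p = 0.06, marital status p = 0.12 to 0.13 (the printed HHE count and percentage do not quite agree), economic status p = 0.39, chronic-disease prevalence among those recorded p = 0.19.

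Mean age and self-rated health both pass a Bonferroni threshold over the seven Table 2 variables (0.05/7 = 0.007).

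**What the unit would change (illustration only).** The document gives no intracluster correlation (ICC) and no count of villages in Hualong; it gives eight communities in total. Assume two villages per arm, so m = 314/4 = 78.5 and the design effect is 1 + 77.5 × ICC.

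| Assumed ICC | Design effect | True type I error of a nominal 5% individual-level test | Power for 0.404 with a village-level t-test on 2 df |
|---|---|---|---|
| 0 | 1.00 | 5% | 49% |
| 0.01 | 1.78 | 14% | 33% |
| 0.02 | 2.55 | 22% | 26% |
| 0.05 | 4.88 | 37% | 16% |

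Type I error is 2[1 − Φ(1.96/√DE)]. Power uses noncentrality 0.404 × √(157/(2·DE)) and critical t = 4.30. With four villages per arm (m = 39.25), type I error would be 10%, 14% and 25% at ICC 0.01, 0.02 and 0.05.

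**The case against.** The strongest defence is that the text describes randomised participants throughout. If field sites are villages, stratifying by site would put both arms in each one. Most of the Table 2 comparisons look random, and sex is almost identical (35.9% against 35.67% male). Table 2 also has slips elsewhere: the arm counts give 187 men and 247 women, the reverse of the printed totals. A coding error in self-rated health, or asking the question after the first education session, is therefore a live explanation. Chronic-disease prevalence does not show a matching gap, though its missingness is unequal. Baseline covariates are collected, matching is promised, and details of the model may sit in an analysis plan that is not shown.

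Much of this stands. A reader might infer that villages were allocated whole; no section says so, and the imbalance does not prove it. A reader might also infer that individual-level analysis is wrong whichever way allocation was done. That does not follow: if individuals were randomised within shared villages, exposure of controls dilutes the effect but leaves the individual-level intention-to-treat test valid. Nor is HHE delivered to whole communities in any full sense. The face-to-face session is for participants and community workers, and the online part is for adults with hearing impairment and their communication partners. Only the posters, and community residents as a named target, clearly reach further.

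What the defence does not answer is age. Miscoded or late-asked self-rated health would not shift mean age, halve its variance or triple the missingness of another variable. Matching does not reveal how the groups were formed.

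**Conclusion.** The concern holds for the imbalance and for the explanation offered. Differences of 46 points in good self-rated health and 3.4 years in mean age, a twofold difference in age variance, and missing chronic-disease status of 8.9% against 29.5% are not plausible results of stratified individual randomisation of about 157 per arm. The small-sample remark does not account for them. This rests on Table 2 as printed and needs no outside figure.

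The cause is not established. Allocation by village, differential enrolment or interviewing, and a data error all remain open, and no one of them need explain everything. It is also not established that HHE participants truly started healthier. The clustering figures show what would be at stake if villages were the unit; they rest on an assumed layout and assumed ICCs and do not measure a demonstrated defect.

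**What to change.** Before the effect analysis, which the protocol says has not yet shown results:

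1. Compare the statistician's allocation list with arm and village, and check how self-rated health was coded and whether it was asked before the T0 session.
2. State the actual unit of allocation and delete the small-sample explanation.
3. Adjust the HHE-control contrast for baseline outcome, age and hearing-impairment severity. Add self-rated health only if it proves correctly coded and measured before the session.
4. If villages were allocated, use an analysis that accounts for village with a small-sample correction. If individuals were allocated, keep the individual-level analysis with site as a stratum, and report control-arm hearing literacy at 24 months as a check on contamination.
5. If allocation was not random, label HHE against control quasi-experimental.

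The cost is an audit of existing records and a few model terms. If few villages were the unit, intervals will be substantially wider. The trial may also have to give up part of its claim to randomisation.
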